# Cooperative pain education and self-management (COPES): study design and protocol of a randomized non-inferiority trial of an interactive voice response-based self-management intervention for chronic low back pain

**DOI:** 10.1186/s12891-016-0924-z

**Published:** 2016-02-16

**Keywords:** Chronic low back pain, Clinical trial, IVR, Non-inferiority trial, CBT, Self-management

## Abstract

**Background:**

The Institute of Medicine report “Relieving Pain in America” recommends the promotion of patient self-management of pain for all people with pain. Given the high prevalence of chronic pain in the US, new strategies are needed to enhance access to cognitive behavioral therapy (CBT) and other evidence-based treatments designed to facilitate self-management of chronic pain conditions. Although CBT is efficacious, many patients have limited or no access to CBT. Technology-assisted delivery of CBT may improve access while maintaining efficacy.

**Methods/Design:**

We describe a randomized non-inferiority trial of interactive voice response (IVR)-based CBT for patients with chronic low back pain. This intervention uses daily IVR monitoring and weekly pre-recorded therapist feedback, based on patient-reported information, to provide treatment for patients at home. A total of 230 patients with chronic low back pain are being identified from a single statewide health system serving US military veterans. Participants are randomized to receive either ten weeks of in-person CBT or IVR-based CBT. The primary outcome is pain intensity as measured by the Numeric Rating Scale immediately post-treatment. Secondary outcomes include pain-related interference, emotional functioning, and quality of life measured immediately post treatment, and 6 and 9 months post recruitment. Exploratory objectives of the study are to examine: (1) potential mediators of impact on clinical outcomes (treatment retention, self-reported skill practice ratings, IVR call adherence, and treatment satisfaction); and (2) moderators of treatment engagement, adherence to therapist recommendations for pain coping skill practice, and effects on clinical outcomes.

**Discussion:**

This non-inferiority trial may identify an alternative to resource intensive in-person CBT that allows many more patients to receive care while also increasing retention of those enrolled in the program.

**Trial registration:**

ClinicalTrials.gov: NCT01025752. Registered 3 December 2009.

## Background

### Need for pain self-management

A recent Institute of Medicine (IOM) report estimates that approximately 100 million people in the US experience chronic pain at any one point in time [1]. Among the IOM committee’s recommendations is the widespread promotion of pain self-management for all people who experience pain. The report highlights the frequent barriers to care experienced by individuals with pain and encourages the development of strategies to address those barriers. Directly relevant to these two recommendations are investigations of novel ways to provide access to evidence-based self-management interventions. Although many interventions exist and individuals with pain may have a variety of preferences, cognitive behavioral therapy (CBT) is a mainstay of pain self-management interventions.

### Chronic pain and CBT

CBT has demonstrated efficacy for reducing pain and improving function in individuals with chronic pain. In a meta-analysis of psychological interventions for CLBP, Kerns and colleagues documented moderate to large effects of CBT and other psychological interventions in reducing pain and pain-related interference [2]. Similarly, a Cochrane review found combined cognitive and relaxation-based treatments were superior to a wait list control condition and resulted in moderate reductions in pain intensity [3].

The overarching goal of CBT is to assist the patient in developing an adaptive problem-solving, self-management approach to pain based on a conceptualization of pain as controllable and a personal attitude of self-efficacy and self-control. An important aspect of CBT is its foundation in a biopsychosocial and multidimensional perspective of chronic pain and the fact that CBT is specifically designed to target reductions in pain, disability, and emotional distress, while improving the patient’s overall quality of life. During therapy, a range of cognitive (e.g., attention diversion, development of coping self-statements) and behavioral (e.g., behavioral activation, activity pacing, relaxation) pain coping skills are taught. Patients are encouraged to practice the skills outside treatment sessions through assignment of specific goals for pain coping skill practice. Goal setting and coping skill practice are important components of CBT. Therapist reinforcement of pain coping skill practice, goal accomplishment, and problem solving, and support when goals are not successfully obtained are also important aspects of treatment.

Although CBT is an effective treatment for reducing pain and enhancing physical and emotional functioning, it has several features that have limited its availability in practice. A typical CBT treatment schedule may require weekly, 50-minute sessions for 6 to 12 weeks. This schedule can put treatment out of reach for patients with limited funds or transportation options, as well as for patients with health and mobility limitations or competing demands that do not easily accommodate weekly appointments. Trained therapists are often unavailable, especially in rural areas, low -income communities, or health systems that are far removed from academic medical centers [4]. As a consequence, CBT therapists only serve a small proportion of patients who might benefit [5]. As a partial solution to these access and cost barriers, new approaches look to mobile health technology, such as interactive voice response, as a way to increase the scale of sustainable programs for patients without the need for 1–1 in-person encounters.

### Interactive Voice Response (IVR)

IVR is an automated telephonic technology that allows patients to report and receive information via their mobile or landline telephone. Calls can be placed at times that are convenient to the patient, and data are collected when patients answer pre-recorded voice prompts using their telephone key pad or voice. Patients also can receive information via IVR such as pre-recorded didactic information regarding pain coping skills or personalized therapist feedback. The therapist is able to monitor a patient’s daily IVR reports and tailor subsequent feedback based on pain-related symptoms, treatment engagement or treatment adherence.

### Use of IVR to deliver treatment

There is emerging evidence that IVR-based interventions are effective for providing education, peer support, and tailored messages to enhance adherence and maintain treatment gains for patients with chronic health conditions [6–10]. Reviews of the broader literature of technology-assisted interventions beyond IVR for conditions like depression and anxiety have concluded that, although technology-assisted interventions are efficacious, some form of therapist contact enhances not just treatment effects, but also treatment retention [11–13]. Within the realm of pain-related research, Naylor and colleagues found that the use of IVR after in-person CBT to reinforce the use of pain coping skills can maintain and even enhance gains made in treatment, reducing the use of opioid-based pharmacotherapy [8, 9, 14]. Also, studies have shown high levels of adherence to daily IVR telephone calls whether participants received payments for calls or not [6, 14]. Despite these promising results, to our knowledge there have been no trials of a solely IVR-based treatment for chronic pain.

### Conceptual framework

#### Non-inferiority trial of IVR-based CBT for chronic pain

When a new treatment promises potential benefits such as improved access, fewer side effects, or lower cost relative to an established treatment, but there is no hypothesized reason to believe that the new treatment is more efficacious, a non-inferiority trial can be used to examine the relative benefits and efficacy of the two alternatives. A new treatment is considered to be non-inferior based on evidence that the decrement in efficacy of the new treatment relative to the established treatment, by a pre-specified margin (called the “non-inferiority margin”) [15]. For example, in a non-inferiority trial of pain management treatments such as the one conducted, if the actual difference in mean pain intensity between IVR-based CBT (IVR-CBT) and in-person CBT is less than the pre-defined non-inferiority margin, IVR-CBT will be judged to be non-inferior to in-person CBT. The primary rationale for this trial is that IVR-CBT offers potential benefits (e.g., improved access, lower patient burden) relative to in-person CBT, wherein the tradeoff of a slight decrement in efficacy can be tolerated in return for enhanced access to care. If IVR-CBT is found to have clinically non-inferior outcomes relative to in-person CBT, it will be recommended for use to patients with chronic low back pain (CLBP) and could be adopted as an alternative to the current, more costly approach.

An important objective in translating CBT to the IVR environment was to promote practice of the pain coping skills through goal setting while retaining the therapist contact and reinforcement that is associated with positive patient outcomes. We sought to leverage the ability of the IVR system to provide brief, automated contact with participants to not only assess skill practice adherence, but to provide a sense of regular contact and to enhance feedback.

### Key intervention components

#### A pedometer-assisted graduated walking program

Participants in both treatment conditions are given a pedometer to facilitate their engagement in the walking component of the treatments. The walking program is progressive and participants are assigned a weekly goal of increasing their average daily step count by 10 % over the prior week’s average step count beginning in week three when the physical activity module is presented in both the IVR and “live” therapist arms of the trial.

#### Patient handbooks

At baseline, participants in both conditions receive handbooks that describe the CBT treatment skills and weekly goals, and contain instructions for using the IVR system and pedometer. For patients randomized to IVR-CBT the handbook information is also made available during IVR calls. Easy accessibility of this information is critical for these patients because they cannot rely on the therapist for its presentation and reinforcement. In the in-person condition, information about pain coping skills is conveyed primarily through the therapist during weekly sessions and the companion handbook contains shortened versions of the pain coping skill explanations contained in the IVR-CBT handbook.

#### Skill practice and meaningful activity goals

Each week, participants are assigned a daily skill practice goal that corresponds to the specific pain coping skill presented in treatment that week (e.g., Week 4: practice deep breathing for 5 minutes each day). The *skill practice goal* for each week is described in the patient handbook for participants randomized to the IVR-CBT condition and is assigned by the therapist during the weekly treatment session for participants randomized to the in-person CBT condition. Participants in both conditions are assigned the same skill practice goals (see Table 1). As participants progress through treatment, they are encouraged to continue practicing skills learned in prior modules. Participants also create their own *goal for engaging in pleasant or meaningful activities* to promote behavioral activation (i.e., planned rewarding or productive activities in order to enhance mood and activity levels). Participants in the IVR-CBT condition are guided in this effort by information in the patient handbook. Participants in the in-person CBT condition collaborate in setting goals with their therapist during treatment sessions.

**Table 1 Tab1:** Treatment modules and goals for CBT and IVR-CBT

Week	Coping Skill	Description	Goals
0	None	Baseline assessment	None
1	Introduction	Present rationale for treatment, explain pain cycle and introduce goal setting.	- Complete one exercise each day in the “Your Guide to Setting Meaningful Activity Goals” section
2	Stretching	Introduce stretching, its benefits, explain acute vs. chronic pain, beliefs about pain and provide suggested stretches to practice.	-Practice stretches provided in the handbook daily
			-Set/ work on meaningful activity goal
3	Movement, Walking & Body Mechanics	Instructions for walking, body mechanics, increasing activity and preventing injuries.	-Practice body mechanics
			-Increase daily steps +10 % of prior week’s steps
			- Set/ work on Meaningful activity goal
			-Continue to practice prior week’s skill
4	Deep Breathing	Instructions for diaphragmatic breathing and its benefits.	-Practice diaphragmatic breathing using CD for 5–10 minutes/day
			-Increase daily steps +10 % of prior week’s steps
			- Set/ work on meaningful activity goal
			-Continue to practice prior weeks’ skills
5	Progressive Muscle Relaxation	Instructions for progressive muscle relaxation and its benefits.	-Practice progressive muscle relaxation using CD
			-Increase daily steps +10 % of prior week’s steps
			- Set/work on meaningful activity goal
			-Continue to practice prior weeks’ skills
6	Identifying Unhealthy Thoughts	Influence of negative thoughts on pain, activities and mood.	-Practice catching unhealthy thoughts
			-Increase daily steps +10 % of prior week’s steps
			- Set/work on meaningful activity goal
			-Continue to practice prior weeks’ skills
7	Balancing Unhealthy Thoughts	Instructions for challenging and changing negative thoughts	-Practice catching and changing unhealthy thoughts
			-Increase daily steps +10 % of prior week’s steps
			- Set/work on meaningful activity goal
			-Continue to practice prior weeks’ skills
8	Time-Based Pacing	Instructions for time-based pacing and its benefits.	-Practice time-based pacing by applying it to one activity daily
			-Increase daily steps +10 % of prior week’s steps
			- Set/work on meaningful activity goal
			-Continue to practice prior weeks’ skills
9	Sleep Hygiene	Common sleep problems and sleep hygiene tips.	-Practice at least one sleep hygiene tip daily
			-Increase daily steps +10 % of prior week’s steps
			- Set/ work on meaningful activity goal
			-Continue to practice prior weeks’ skills
10	Planning for the Future	Relapse prevention; reviewing goals and accomplishments, managing relapse and pain flare ups.	- Complete 1 section of the pain flare prevention handout daily.
			-Increase daily steps +10 % of prior week’s steps
			- Set/work on meaningful activity goal
			-Continue to practice prior weeks’ skills

#### IVR assessment

Participants in both conditions receive daily automated calls from the IVR system. Calls are scheduled to occur each evening at the same time within the daily assessment window of 6:00 PM-10:00 PM in order to ensure that each call represents a 24-hour reporting period. Calls are scheduled at a time of the participant’s choosing. Participants are also able to connect directly with the Department of Veterans Affairs (VA) Veteran Crisis Line. The crisis line is staffed 24-hour a day and offers callers (or those who use confidential chat or text) support, crisis response, and facilitates follow-up in-person care at a veteran’s local VA medical center.

#### Weekly therapist feedback

Participants in the IVR-CBT condition receive a weekly, two to five minute pre-recorded personalized message from their therapist via the IVR system. On the last day of each week participants are told that they have a message from their therapist. This message may be accessed and replayed as often as the participants want. If participants miss the call that contains the feedback message, they are prompted to listen to the message during their next call. Participants and therapists may record messages to one another on the IVR system at any time during treatment. This allows participants and therapists to obtain clarification or feedback on specific topics and avoid frustration that may impair progress or prompt dropout.

## Methods/Design

This randomized controlled non-inferiority trial includes assessment of outcomes at baseline, post-treatment (i.e., 3 months), 6 months and 9 months (See Fig. 1) with post-treatment being the primary timepoint. The aims of the study are:Aim1: To determine whether IVR- CBT for chronic low back pain is non-inferior or “not unacceptably worse” [15] than the gold standard in-person treatment. The primary outcome is pain intensity as measured at post-treatment by the 11-point [0 (no pain) to 10 (worst pain imaginable)] Numeric Rating Scale (NRS) for pain. The non-inferiority margin was set at one point on the NRS.Aim 2: To determine whether IVR-CBT enhances participants’ physical and emotional functioning, and health-related quality of life immediately post-treatment and each follow-up relative to in-person treatment.Aim 3: To determine whether treatment groups differ with respect to important mediators of outcomes, including treatment dropout rates, self-reported skill practice ratings, IVR call adherence, and treatment satisfaction.Aim 4: To identify key moderators of improvements in treatment outcomes including age, sex, race/ethnicity, number of pain sites and location, medication use*,* and psychiatric comorbidities.

**Fig. 1 Fig1:**
[figure not shown]
Study recruitment, enrollment, treatment, and assessment processes

Eligible patients are randomized to receive either standard in-person CBT for CLBP or IVR-CBT. This study was approved by Institutional Review Boards at Yale University School of Medicine and the VA Connecticut Healthcare System (VACHS).

### Eligibility

#### Experimental subjects and controls

Participants are 230 patients with CLBP receiving treatment at the VACHS. Specific eligibility criteria include: 1) presence of at least a moderate level of pain (i.e., pain intensity rating of ≥ 4 on the 0 to 10 NRS) for a period of ≥ 3 months; 2) diagnosis of a low back pain condition in the electronic health record (EHR); 3) absence of a medical or psychiatric condition that could impair participation (e.g., severe COPD, terminal cancer, active substance abuse, psychosis, suicidality or severe depression Beck Depression Inventory-II score >28 ); 4) self-reported ability to walk at least one block without chest pain; 5) absence of dementia defined by St. Louis University Mental Status examination (SLUMS); [16] 6) absence of surgical interventions for pain during participation in this study (participants undergoing surgery will be discharged from the study in order to maintain the integrity of the active treatments); 7) availability of a touch-tone landline or mobile telephone; and 8) absence of any sensory deficits that would impair participation (e.g., hearing loss to a degree that telephone usage is not possible).

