#### Randomization

Eligible participants are randomized to either in-person CBT or IVR-CBT immediately after completing the baseline assessments. The study research assistant enters the participant’s demographic information and stratification factors into TrialDB, which holds the randomization schedule and is masked from users thereby enabling concealed allocation. The treatment allocation ratio is 1:1 using a permuted stratified block design with variable block size. Randomization is done within strata defined by patients’ distance from the VACHS-West Haven campus (<10, 11–25, 26 or greater miles) and cause of low back pain as determined by the study nurse based on EHR review (non-specific low back pain, low back pain with a radicular component, or pain associated with other specific spinal causes) [18]. The research assistant informs a study therapist of the participant’s treatment assignment.

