#### Outcomes

Survey outcomes are assessed at 4 time points, baseline, post-treatment, and 6 and 9 months post baseline. Participants are given up to 14 weeks to complete treatment in order to accommodate rescheduled sessions due to vacations, illness or travel difficulties. Post-treatment data are collected when a participant completes treatment or at 15 weeks post-baseline regardless of whether the participant has completed treatment. Survey outcomes are assessed using the TrialDB system, which allows participants to complete the self-report questionnaires online via a secure web-based interface. Participants who do not have an Internet connection may come to the medical center to complete the measures via TrialDB or complete a paper version of the measures and return them by mail. IVR outcomes will be assessed daily during the baseline week and over the 10 treatment weeks.

Measures were selected based on the Initiative on Methods, Measurement and Pain Assessment in Clinical Trials (IMMPACT) recommendations [23], which called for the assessment of multiple domains of the pain experience in all pain treatment trials and recommended measures based on their psychometric properties and respondent burden. These measures are consistent with CONSORT guidelines for non-inferiority trials [24] that recommend that outcome measures be similar to those used in studies to establish efficacy of the reference treatment.

*Primary Outcome - Pain intensity:* We assess participants’ average pain intensity over the past week via survey, at the four outcome assessment points using the Numeric Rating Scale of pain intensity (NRS-I) [25] an 11-point numeric rating scale (0 = no pain, 10 = worst pain imaginable). The primary outcome is the average weekly pain intensity at post-treatment.

*Secondary Outcomes – Pain intensity* will also be assessed daily during the trial via the IVR system using the NRS scale. Subjects will have a maximum of 77 daily scores: 7 daily calls for the baseline assessment week and 7 daily calls for each of the 10 weeks of treatment. We will use these scores to compute weekly means for each subject. The mean of seven daily assessments has been found to provide reliability in excess of 0.90 [26].

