#### Analysis

We present below the analysis of primary and secondary outcome measures only. Analysis of primary and secondary outcomes will employ linear mixed-effects models for longitudinal data, which will account for the clustering induced by repeated measures on individual patients. Mixed effects models make use of all available measurements on subjects and provide valid inferences even in the presence of missing data as long as the missingness is at random. Data from different subjects are assumed to be independent, while the correlation structure of the repeated measurements within subjects is modeled via parameterization of the covariance structure.

Between-group comparisons of the effectiveness of IVR-CBT and in-person CBT at each assessment time point will be conducted. Each of these comparisons can be tested separately within the same mixed-effect model using a treatment dummy variable, time dummy variables, and treatment-by-time interaction terms and appropriate contrasts. The outcome variable in each model will be the outcome at the follow-up time points, with the baseline value of the outcome and the stratification variables included as covariates in the model. Results will be summarized as LS- means (and their 95 % confidence intervals) within and between treatment groups at each time point. Non-inferiority will be demonstrated by the upper limit of the 95 % confidence interval for the LS-mean pain difference between IVR-CBT and in-person CBT *at post-treatment* being less than 1. Following CONSORT recommendations [24], non-inferiority analyses will be conducted both on a *per protocol* (e.g., having completed 3 weeks of treatment which is considered a dose of treatment) basis and an *intent-to-treat* basis. All other analyses will be conducted according to intent-to-treat basis, that is, by considering patient group status as randomized.

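### Pain surgery after randomisation is written as an eligibility criterion with discharge from the study, which conflicts with the outcome-collection rule and weakens the intent-to-treat non-inferiority analysis

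*Protocol article*

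**What the plan says.** All references are to the protocol article.

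- **Eligibility (Experimental subjects and controls), criterion 6** requires "absence of surgical interventions for pain during participation in this study" and adds that "participants undergoing surgery will be discharged from the study in order to maintain the integrity of the active treatments".
- **Randomization:** "Eligible participants are randomized to either in-person CBT or IVR-CBT immediately after completing the baseline assessments".
- **Outcomes:** post-treatment data are taken when treatment is completed or "at 15 weeks post-baseline regardless of whether the participant has completed treatment". Surveys follow at 6 and 9 months.
- **Analysis:** the non-inferiority comparison is run both per protocol and by intent to treat. The per-protocol example is "having completed 3 weeks of treatment which is considered a dose of treatment", and surgery is not mentioned. For the rest, "All other analyses will be conducted according to intent-to-treat basis, that is, by considering patient group status as randomized". In the mixed model, "The outcome variable in each model will be the outcome at the follow-up time points", with baseline as a covariate. Such models are said to "provide valid inferences even in the presence of missing data as long as the missingness is at random".
- **Treatment attendance and drop out** and **Missing data:** reasons for dropout and missing data are collected prospectively, and losses are compared by reason and by rate between arms. Baseline predictors of loss become covariates. Multiple imputation is available if missingness proves problematic.

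No section says that a participant discharged for surgery is still surveyed, or how that participant enters the intent-to-treat analysis.

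**The concern.** A criterion about surgery during participation cannot be checked at entry. It can only act on people already randomised, and the article removes them from the study, not merely from treatment. Staff then face two instructions for the same person: a participant operated on in week 8 is out of the study under Eligibility, yet due a post-treatment survey under Outcomes.

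Surgery for pain is plausibly linked to pain intensity, the primary outcome, and it is foreseeable in this population. Recruitment covers nerve compression, two of the three back-pain strata are radicular pain and specific spinal causes, and routine care continues uninfluenced by study staff. If removals are related to pain and differ between arms, the intent-to-treat estimate of the IVR-CBT minus in-person difference is distorted. The per-protocol set offers no independent protection: the week-8 participant satisfies the 3-week example but has no post-treatment value. Outcomes never collected cannot be recovered at the analysis stage.

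**Working it through.** **1. The plan's own figure.** Sample size calculation gives margin 1, SD 2.45, true difference 0, one-sided alpha 0.025, power 80%, 15% losses and 230 in total. Per arm, n = 2 × (1.960 + 0.842)² × 2.45² / 1² = 94.2, so 95. Then 95/0.85 = 111.8, so 112 per arm and 224 in total. A t-based calculation gives 96, then 113 per arm and 226 in total. Both are within 3% of 230, so the sample size is not in dispute.

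**2. Precision.** Evaluable per arm: 115 × 0.85 = 97.75. SE = 2.45 × √(2/97.75) = 0.350. Power at a true difference of 0 is 81.4%.

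**3. Who is affected.** For the primary test, only participants operated on before their post-treatment survey (week 15 at the latest). Once discharged they have no follow-up value at any time point, so they contribute no outcome to the model unless imputed. Someone operated on later keeps the primary outcome and loses only the later surveys.

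**4. Bias.** Let a proportion p of an arm be removed, whose unrecorded scores would average D points above the rest. If the rest average m, the full-arm mean is m + pD and the observed mean is m. The observed difference is therefore off by

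bias = −D × (pI − pC),

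where pI and pC are the removal rates in IVR-CBT and in-person CBT. A negative value favours IVR-CBT. With b the size of a bias in that direction, the one-sided error at a true difference equal to the margin is Φ(−1.96 + b/0.350), holding the SE fixed.

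The documents give no surgery rate and no score gap, so every row below is an assumption:

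| IVR-CBT v in-person | D | Bias | One-sided error |
|---|---|---|---|
| equal rates, equal D | any | 0 | 2.5% |
| 2% v 1% | 2 | −0.02 | 2.9% |
| 6% v 3% | 2 | −0.06 | 3.7% |
| 10% v 5% | 3 | −0.15 | 6.3% |
| 5% v 10% | 3 | +0.15 | 0.8% |

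The last row is the fourth mirrored: Φ(−1.96 − 0.15/0.350) = Φ(−2.39). A negative D also reverses the sign.

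**5. Power.** If surgical removals come on top of the 15% allowance, the evaluable number is 115 × (0.85 − s). For s = 2%, 5% and 10% this is 95.5, 92.0 and 86.3 per arm, with power 80.5%, 79.1% and 76.4%. The effect is modest.

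**The case against.** The strongest reply is that the texts are in tension but not strictly incompatible. The Outcomes rule speaks of unfinished treatment, not of leaving the study. The intent-to-treat wording speaks of group as randomised and does not promise an outcome from everyone. Non-collection after discharge is itself an inference, although it is the plain reading and no other text offsets it. The plan also has safeguards: reasons for loss are recorded and compared by arm, and imputation is available and could draw on the daily pain scores, although the article does not say that it will. These points stand, and they lower the severity. They do not remove the problem. Comparing losses changes only interpretation, the imputation is conditional, and neither establishes missingness at random.

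A reader might infer more than the documents support:

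- *That the rule biases the trial towards non-inferiority.* This needs more removals, with worse pain, in IVR-CBT. Nothing in the article indicates such an imbalance.
- *That data already collected are deleted, or that these participants leave both analysis sets altogether.* No text says so.
- *That criterion 6 should simply be struck out.* Surgery already planned could be identified at screening, since the study nurse abstracts back-pain treatments from the health record. Deletion could change an entry rule that nobody has questioned.
- *That retaining these participants is the conservative choice.* Their retained scores would be post-surgical and could be higher or lower. If IVR-CBT failures had surgery and improved, retention would also narrow the difference between arms.

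**Conclusion.** The point holds as a conflict over who is followed and analysed for the primary endpoint. A post-randomisation event sits in the eligibility list, and its stated consequence is at odds with the outcome-collection rule and undermines the intent-to-treat analysis. For participants operated on before the post-treatment survey, the loss may not be at random, and the planned safeguards mitigate this without curing it.

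The case does not rest on a large bias. Across the assumed scenarios with more removals from IVR-CBT, the bias is about 0.02 to 0.15 NRS points against a margin of 1, and the one-sided error about 2.9% to 6.3%. The upper end needs surgery to be common, twice as frequent in IVR-CBT and associated with a 3-point gap. The direction is not determined by the documents. The stated sample size reproduces and is unaffected.

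**What to change.** Reconcile Eligibility, Outcomes and Analysis:

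1. Separate any surgery-related entry criterion that can be checked at screening from the rule for surgery after randomisation, and take the latter out of the eligibility list.
2. Replace discharge from the study with wording that keeps participants who have surgery in survey follow-up (post-treatment, 6 and 9 months) and in their randomised arm for the intent-to-treat analysis.
3. Record surgery as a post-randomisation event and report its count and timing by arm.
4. State explicitly how surgery is handled in the per-protocol set or in a sensitivity analysis, since the 3-week example does not cover it.

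Whether study treatment continues after surgery is for the investigators and is not addressed here.

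The cost is protocol wording and survey follow-up of the participants concerned. The required sample size does not change. The downside is that some retained outcomes will reflect the effect of surgery, in either direction, so the intent-to-treat result should be read alongside the analysis in item 4.
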